# A digital intervention to reduce home-office workers’ sedentary behaviour: protocol for the evaluation of the Click2Move programme, a cluster randomised controlled trial

**DOI:** 10.1186/s12889-025-21598-7

**Published:** 2025-01-30

**Keywords:** Home-office work, Hybrid office work, Digital intervention, Sedentary behaviour, Protocol

## Abstract

**Background:**

A new paradigm of hybrid working exists, with most office workers sharing their work between the office and home office environment. Working from home increases time spent or prolonged sitting, which is associated with an increased risk of chronic disease. Interventions to reduce sitting time, specifically designed for both the office and home-office environments, are required to address this growing public health issue. This study presents a protocol to evaluate the effectiveness of a digital intervention (Click2Move) to reduce sitting time and improve employees’ health and occupational wellbeing among hybrid office workers.

**Methods:**

A two-arm cluster randomised controlled trial will be undertaken among hybrid office employees. In total, 200 employees will be recruited across four companies across Europe (The Netherlands, Spain, Ireland, and Slovenia). Participants within each company will be randomly allocated to the intervention or control group at the unit/cluster level. The intervention group will receive the novel multicomponent Click2Move intervention (including environmental, organisational, and individual strategies) for 12 months, and the control groups will maintain their usual work practices. The primary outcome will be occupational sedentary time measured via activPAL^3TM^ at baseline and at 3, 6 and 12 months follow-up. Secondary outcomes will include device-based (activPAL^3TM^) and self-reported (Global Physical Activity Questionnaire and Workforce Sitting Questionnaire) physical activity and sedentary behaviour; self-reported musculoskeletal disorders (Standardised Nordic Questionnaire) and pain (Numeric Rating Scale); self-reported presenteeism and absenteeism (Health and Work Performance Questionnaire), job satisfaction (Need for Recovery scale) and fatigue (single-item 5-point Likert scale). Focus groups will be conducted with employees post-intervention. Linear mixed models, accounting for covariates, will be employed to determine the effects of the intervention. Additionally, we will perform a full process evaluation analysis.

**Discussion:**

The proposed study will offer a comprehensive evaluation of a digital intervention aimed at reducing sedentary behaviour among hybrid office workers, offering practical solutions to enhance the health, wellbeing and productivity of a growing segment of the workplace.

**Trial registration:**

ClinicalTrials.gov NCT06247228. Registered 30 January 2024.

**Supplementary Information:**

The online version contains supplementary material available at 10.1186/s12889-025-21598-7.

## Background

The importance of reducing and limiting daily sedentary behaviour (SB) has been well acknowledged in existing guidelines for promoting health in addition of achieving the physical activity (PA) recommendations for health (at least 75–150 minutes a week of vigorous PA intensity, or an equivalent combination of moderate-intensity and vigorous-intensity activity throughout the week) [1]. While being highly active (60–75 minutes/day of moderate to vigorous PA (MVPA)) may attenuate the health-related risks of high levels of sedentary time (> 8 hours/day) [2, 3, 4], they may not be fully eliminated [5]. Although PA can be undertaken in a range of domains, including occupation, transport, household or leisure settings, a very low proportion of individuals (< 5% of population) perform the minimum recommended levels of MVPA to maintain health [2]. This is particularly relevant among office workers who spend 72.5% of their working hours in sedentary time [6], with those who spend a larger proportion of their time sitting at work also spending more time sitting during leisure time [7]. Prolonged occupational SB has been associated with health and work-related outcomes, including musculoskeletal disorders [8], job satisfaction, fatigue [9], and presenteeism [10].

The COVID-19 pandemic has drastically transformed work culture towards greater flexibility concerning work location, time, and organization [11]. In Europe, approximately 40% of employees began working from home due to the pandemic [12]. Since then, the new hybrid work paradigm, combining office work and home-office work, has been predominantly used among desk-based occupations [13]. Emerging research suggests that home-office workers are more sedentary and less physically active than traditional office workers [14, 15]. This could be attributed to reductions in activity achieved through commuting to and from work, overlapping online meetings, and having fewer face-to-face social interactions [16] which result in longer sitting hours with fewer breaks [17]. Due to the increased time spent in prolonged SB when working from home, employees may be at an increased risk of developing musculoskeletal disorders [18, 19, 20], poor health and work-related outcomes such as well-being and productivity [21, 22, 23]. Therefore, occupational interventions designed to reduce and fractionate prolonged sedentary periods in home-office and hybrid workers are required [15, 24].

Recent systematic reviews have reported that multicomponent interventions, including two or more of the following aspects: (i) environmental changes (e.g., sit-stand desks or active workstations); (ii) workplace policy changes (e.g., walking strategies such as incidental movement); or (iii) information and counselling interventions (e.g., providing educational material or self-measurement activity) are most effective in reducing SB among office workers than single-component interventions [25, 26, 27, 28]. In particular, interventions that incorporate sit-stand desks appear more effective than interventions without, but they may not be suitable for hybrid jobs due to the high-cost implications [29]. Moreover, effective behavioural change strategies at the workplace are not necessarily to be feasible in this new dynamic paradigm, which implies a constant change in the social and physical environment.

Reducing and breaking up prolonged SB when working from home is an emerging yet unexplored research area. Therefore, it is important to engage stakeholders and end users in developing and evaluating tailored interventions that address the real needs of the changing work environment, through a participatory research approach. Explorative studies have identified promising strategies to support workers in the home environment through a range of behavioural strategies, such as feedback on activity patterns, self-monitoring activity behaviours, educational material, prompts, motivational messages, role modelling, awards or incentives [27, 30, 31], with the findings of these studies highlighting digital technologies as a potential mode of delivery [31]. Technological advancements not only enable the delivery of information but also mediate organizational support and social influences [32], a challenge in the home office context [24]. Additionally, they provide feedback based on self-reported data and offer decision prompts through novel interfaces and devices, making interventions more adaptive to the user’s context [32], especially within the diverse landscapes of hybrid workers. In recent years, some studies have demonstrated their effectiveness on incorporating digital elements for delivering workplace strategies in reducing workplace SB and its harmful effects [27, 33], however, less is known on how digital elements may enhance interventions for reducing and breaking SB on hybrid contexts [27].

Consequently, the primary aim of this study is to evaluate the effectiveness of a digital intervention (Click2Move (C2M)) among home-office workers in reducing occupational SB. This study will also aim to evaluate changes in other PA and SB patterns (occupational behaviours and leisure time behaviours), impacts on musculoskeletal health and work-related outcomes (i.e., absenteeism, presenteeism, occupational fatigue and job satisfaction). Additionally, this study will conduct a process evaluation of the implementation of the C2M intervention.

## Methods

The present protocol has been developed and reported based on the Standard Protocol Items: Recommendations for Interventional Trials (SPIRIT) [34].

### Trial design

A multicentric, two-arm cluster randomised controlled trial (RCT) will be undertaken. Participants will be randomised by cluster to receive the intervention (C2M) or act as a unit in the control group and maintain their usual work. This study will be conducted, analysed, and reported according to the Consolidation Standards of Reporting Trials (CONSORT) statement for cluster-RCTs [35]. The trial has been registered at ClinicalTrials.gov Protocol Registration and Results System (NCT06247228).

### Study setting

Companies with home-office policies will be selected from countries of the C2M project consortium (i.e., Spain, Ireland, The Netherlands, and Slovenia) representing different geographic regions, cultures, and legislations across Europe.

### Eligibility criteria

#### Companies

Companies having different units, with 50 or more employees, and applying home-office policies will be included in the study. The list of potential companies was provided by the European Network for Workplace Health Promotion, which is also involved in the C2M project. All those companies involved in other initiatives to reduce SB will be excluded from the study.

#### Participants

Participants must be adults aged 18–65 years old with a desk-based job, working from home at least two days per week. Furthermore, participants must be able to walk without the use of an assistive device or requiring assistance from another person. Participants who are unable to read and understand the language native to the country in which they are residing, or employees with an end date for employment prior to the study completion date, will be excluded from the study. Participants using other devices for activity tracking such as a smartwatch will be eligible for inclusion.

### Recruitment

Within each participating country, each national coordinator will send an initial email to potential country-representative companies from a variety of sectors in their own language with an accompanying flyer and a short company eligibility survey. The companies who express their interest to participate, and are eligible for participation, will receive an email to organise an appointment with the national research team. During this meeting, the project will be explained in greater detail and any possible doubts or issues the company may have will be discussed. If a commitment is made, the company will have access to the following promotional materials: study presentation, a flyer with the key study information and elements, study information email template and the ethical information statement. The study will be advertised by the company, through an internal newsletter and meetings, to employees that undertake hybrid working. Moreover, employees will receive an invitation email by the company manager with the pre-screening eligibility survey, the information statement, and the informed consent form. Those employees who meet the inclusion criteria and sign the informed consent digitally through the pre-screening eligibility survey, will be contacted to thank them for their interest and will be invited to a meeting to examine baseline measures. Figure 1 describes the flow chart for all elements of the C2M study.

**Fig. 1 Fig1:**
[figure not shown]
Click2Move study flow chart

### Allocation and blinding

After completion of the baseline measurements, participants will be randomised by clusters (units) 1:1, to either intervention or control group to reduce the risk of contamination. The randomisation will be performed by the principal investigator ([name]). Participants will be informed of the group they have been allocated to by email. For the intervention group, this email will also include the link to download the C2M App, an infographic containing a usage tutorial of the programme with frequently asked questions, and a video tutorial on the C2M programme. Only participants allocated to the intervention group will be invited for another meeting within the company, which will take place one week after receiving the group allocation email.

Given the nature of the study, it will not be possible to blind participants to their allocated group. However, the randomisation will be taken at the unit level to reduce the risk of contamination between groups (i.e. intervention and control groups will be located at different units). Measurement team members will not be blinded to group allocation.

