### Sample size

The sample size was based on detecting a relevant effect on the primary outcome, sitting time during working hours. Based on an assumed mean reduction of 55.92 min/day sitting in the intervention group and a standard deviation in both groups of 90 min/day [36], a power of 80%, a two-sided alpha of 0.05, and a 20% dropout rate, a total of 200 participants across four companies at baseline will need to be recruited. Within each company, randomization in the intervention group or control group takes place at the unit level (clusters) through a hierarchic clustering between units in a company, assuming a low intra-cluster correlation coefficient (ICC) of 0.05 for the unit and 0.2 for the company. Per company, one control unit and one intervention unit will be included with the total number of participants being equal per company (*n* = 50). The total sample size will be equally distributed across both conditions (25 in the intervention group and 25 in the control group in each company in each country).

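### The principal investigator draws the allocation of only eight units and measurement staff are unblinded; an independent coded draw and arm-masked data processing would be cheap safeguards

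*Protocol article*

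**What the plan says.** The section Allocation and blinding of the protocol article fixes four things.

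- Order and unit of allocation: "After completion of the baseline measurements, participants will be randomised by clusters (units) 1:1".
- Who allocates: "The randomisation will be performed by the principal investigator".
- Participants: "it will not be possible to blind participants to their allocated group".
- Staff: "Measurement team members will not be blinded to group allocation".

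The Sample size section sets the scale: "Per company, one control unit and one intervention unit will be included", with "25 in the intervention group and 25 in the control group in each company in each country". Four companies therefore give eight units and four within-company draws, or 2^4 = 16 possible allocations.

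The primary outcome, occupational sedentary time, is recorded by activPAL. Under PA and SB outcomes, participants log working hours, work location and removal times in a diary, and the files are then reduced with named software by a published procedure. The article does not say who does this processing. Under Data management, the data are pseudonymised and held centrally.

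**The concern.** The person leading the trial has an interest in the result and performs the allocation. With four binary draws, each one decides a quarter of the comparison, so a single influenced draw would not average out as it might among many clusters. By that point baseline measurements exist for every unit.

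The second element is outcome handling. Occupational sitting time is not a raw device readout: it depends on which hours count as work, which periods count as removal, and how files are cleaned. Participants cannot be masked, so masking these steps is one of the few protections still available. The article states that the measurement team is unblinded and does not mention masked processing.

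Both are stated arrangements and both can be avoided. At stake is whether an outside reader can be sure that neither the allocation nor the derivation of the primary outcome was influenced by knowledge of the units or arms.

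**Working it through.** **Inputs from Sample size.** Effect: "assumed mean reduction of 55.92 min/day sitting in the intervention group". Variability: "a standard deviation in both groups of 90 min/day". Unit ICC 0.05, company ICC 0.2, 25 people per unit at baseline, 20% dropout, 80% power, two-sided alpha 0.05.

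**1. The plan's own figure.** Per arm, 2 × [90 × (1.960 + 0.842) / 55.92]² = 40.7, rounded up to 41, so 82 in total. With 20 completers per unit the design effect is 1 + 19 × 0.05 = 1.95; 82 × 1.95 = 159.9, or 160; 160 / 0.80 = 200. The stated total is reproduced using the unit ICC alone, so 90 and 0.05 are the right inputs for what follows. The company ICC plays no part because arms are compared within company.

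**2. A genuine random draw.** Expected allocation bias is 0. Chance imbalance in true unit means over four pairs has SD √(2 × 405 / 4) = 14.2 min/day and mean absolute size 11.4 min/day, where 405 = 0.05 × 90² is the between-unit variance.

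**3. All four draws steered, true unit means known exactly.** Unit SD = √0.05 × 90 = 20.1. The expected gap between two units of a company is 2 × 20.1 / √π = 22.7 min/day. One steered company would contribute 22.7 / 4 = 5.7.

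**4. All four draws steered on observed baseline means.** This is the more realistic route, because only sample means of 25 people would be available. Sampling variance of a unit mean = 8100 × 0.95 / 25 = 307.8. Reliability = 405 / (405 + 307.8) = 0.568. Lasting bias = 22.7 × √0.568 = 17.1 min/day, which is 31% of 55.92 and 57% of the 29.9 min per 8 h workday given under Development. One company would contribute 17.1 / 4 = 4.3. With 20 people per unit the figure is 16.3; removing the company share from the residual variance gives 17.2 to 18.0.

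**5. Range over the unit ICC** (0.01 and 0.10 are assumed; 25 people per unit):

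| Unit ICC | Unit SD | Bias, true means known | Reliability | Bias, observed means |
|---|---|---|---|---|
| 0.01 | 9.0 | 10.2 | 0.202 | 4.6 |
| 0.05 | 20.1 | 22.7 | 0.568 | 17.1 |
| 0.10 | 28.5 | 32.1 | 0.735 | 27.5 |

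**6. With baseline adjustment, observed-means route.** The expected observed baseline gap is 2 × √712.8 / √π = 30.1. At an assumed slope of 0.5 the residual is 17.1 − 15.1 = 2.0 in favour of the intervention. At 0.7 it is 17.1 − 21.1 = −4.0, against it.

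**7. Outcome handling.** The document contains no figure from which to compute a bias from unblinded staff. None of the numbers above covers it.

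**The case against.** The strongest reply is that the article says the units are randomised, and naming who runs a draw does not show that it can be steered. That stands. Sequence generation and concealment are details that an article commonly leaves to the full protocol, so their absence here is no finding.

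A reader might infer that the principal investigator sees unit means before allocating. The text does not support this; it gives only the order of events. That order is itself a strength, because consent and baseline before allocation protect a cluster trial against recruitment bias.

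A reader might also take 23 min/day as the upper limit of the harm. It is an average that assumes deliberate steering in all four companies, exact knowledge of true unit means and no baseline adjustment. The Data analysis section does not name baseline sitting as a covariate, but its covariate list is open-ended and baseline is one of four measurement occasions. In a change-from-baseline analysis (slope 1), steering on observed means would even work against the intervention: 17.1 − 30.1 = −13.0 min/day.

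On blinding, the outcome comes from a device, the diary is filled in by participants, and the measurement team may not be the people who process the files. This narrows the route to device set-up, diary-based windows and cleaning. It does not close it, since masked processing is not stated.

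What survives against the reply is modest. Baseline adjustment corrects for baseline sitting only. It does not correct for other knowledge, such as which unit's managers seem more receptive. That part cannot be quantified.

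**Conclusion.** The point holds as a cheap safeguard worth adopting, not as evidence of bias. The article assigns the draw of eight units to the principal investigator and leaves measurement staff unblinded, and neither is necessary. No misuse is shown or alleged.

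If all four draws were steered on observed baseline means, the plan's SD and unit ICC imply about 17 min/day before baseline adjustment and roughly 2 to 4 in absolute size with it. This rests on unit differences that persist to follow-up, 25 people per unit, and assumed slopes of 0.5 to 0.7. The unadjusted figure is sensitive to the unit ICC: 5 to 28 min/day over 0.01 to 0.10, or 10 to 32 with perfect knowledge. These sizes concern allocation only and should not be attached to the unblinded measurement team.

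**What to change.** Keep baseline measurement before allocation. List the eight units by code and have a consortium member with no role in recruitment, delivery or measurement draw the allocation within each company by computer, with the seed recorded. Process activPAL files and diaries (working-hour windows, removal times, cleaning) under the existing pseudonymised IDs without the arm code, and lock the processed data before unmasking. If allocation has already taken place, document how the draw was made and apply the masked processing to files not yet handled.

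The cost is some coordination between sites and preparation of files without the arm label. The article does not identify a statistician for the task, so the consortium would need to name a suitable person. The target of 200 participants, the visits and the intervention are unchanged.

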### Sample size

The sample size was based on detecting a relevant effect on the primary outcome, sitting time during working hours. Based on an assumed mean reduction of 55.92 min/day sitting in the intervention group and a standard deviation in both groups of 90 min/day [36], a power of 80%, a two-sided alpha of 0.05, and a 20% dropout rate, a total of 200 participants across four companies at baseline will need to be recruited. Within each company, randomization in the intervention group or control group takes place at the unit level (clusters) through a hierarchic clustering between units in a company, assuming a low intra-cluster correlation coefficient (ICC) of 0.05 for the unit and 0.2 for the company. Per company, one control unit and one intervention unit will be included with the total number of participants being equal per company (*n* = 50). The total sample size will be equally distributed across both conditions (25 in the intervention group and 25 in the control group in each company in each country).

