### Intervention

#### Development

The C2M intervention has been developed from a participatory research approach, with academics working alongside other stakeholders [37]. The development process of the C2M intervention includes a systematic review [27], two qualitative studies, including employers and employees [38] and a Delphi study with experts on occupational health and PA promotion [31]. Moreover, C2M followed the new Medical Research Council (MRC) framework on the development of complex interventions to improve health [39, 40]. Firstly, a systematic review and meta-analysis was conducted to examine the effectiveness of digital workplace interventions to reduce time spent in SB in office workers [27]. Nineteen randomised controlled trials were included in the systematic review, eleven of which were used in the meta-analysis. A wide range of digital elements and working strategies were described among the included studies. Delivery of information and educational materials through text messages, e-newsletters, websites or videos for increasing knowledge and awareness were the most common digital workplace strategy. Scheduled prompts to break SB or participate in PA delivered via computer screens and mobile phone applications were the second most common digital workplace strategy. The results of the study indicated that multicomponent digital interventions, including elements at organisational, environmental, and at the individual level are effective to reduce workplace SB, presenting a reduction of 29.9 min/8 h workday [27].

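### The stated 80% power allows for the unit ICC but not for having only eight units in four company pairs; on the plan's own inputs, unadjusted power is about 49–53%

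*Protocol article*

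**What the plan says.** All the figures stand in the Sample size section of the protocol article.

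- **Effect:** "Based on an assumed mean reduction of 55.92 min/day sitting in the intervention group".
- **Variability:** "a standard deviation in both groups of 90 min/day".
- **Error rates and dropout:** "a power of 80%, a two-sided alpha of 0.05, and a 20% dropout rate".
- **Size:** "a total of 200 participants across four companies at baseline will need to be recruited".
- **ICCs:** 0.05 for the unit and 0.2 for the company.
- **Layout:** "Per company, one control unit and one intervention unit will be included with the total number of participants being equal per company", with 25 participants per unit.

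Allocation and blinding confirms that units are randomised 1:1. Data analysis plans linear mixed models with country among the covariates. There is one company per country, so adjusting for country also adjusts for company.

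**The concern.** In a cluster trial, the precision of the treatment effect depends on how many units there are as well as on how many people. A design effect inflates the variance for correlation within units. It does not allow for the fact that the between-unit variance must itself be estimated, here from very few units. With one unit per arm in each of four companies, the information on that variance is the spread of four differences.

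If the power claim takes no account of this, the trial will be read as 80% powered when it is not. A null result on occupational sitting time would then look like evidence against the intervention, although the design had roughly an even chance of missing the full planned effect.

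**Working it through.** **Inputs** (all from Sample size): effect 55.92 min/day, SD 90, two-sided alpha 0.05, power 80%, dropout 20%, unit ICC 0.05, company ICC 0.2, and eight units of 25 at baseline, which leaves 25 × 0.8 = 20 completers each.

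**1. Reproduce the plan's figure.**
- Individual-level n per arm = 2 × (1.96 + 0.8416)² × 90² / 55.92² = 40.7, rounded up to 41.
- Design effect = 1 + (20 − 1) × 0.05 = 1.95.
- 41 × 1.95 = 79.95, so 80 per arm and 160 in total; 160 / 0.8 = 200.

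The other routes tried do not give 200. No design effect gives 103, a design effect on 25 per unit (2.20) gives 225, and an ICC of 0.2 in the design effect gives 490. The stated 80% is therefore the large-sample normal result.

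**2. Standard error of the treatment contrast.** The contrast is the mean of four within-company differences between unit means, so company variance cancels:

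SE = 90 × √[2 × (u + w/20) / 4], where u is the unit share and w the residual share of the variance.

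The article does not say whether the SD of 90 includes company variance, so three readings are shown:
- A: u = 0.05, w = 0.95.
- B: u = 0.05, w = 0.75 (company share of 0.2 removed).
- C: u = 0.04, w = 0.76 (unit ICC taken as a share of within-company variance).

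**3. Power at 55.92 min/day.** Degrees of freedom are 4 − 1 = 3 and the critical t is 3.18. Power comes from the noncentral t with noncentrality 55.92 / SE. For 80% power with 3 df the noncentrality must be 4.256, so the detectable effect is 4.256 × SE.

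| Reading | SE (min/day) | Noncentrality | Power, normal | Power, 3 df | Effect for 80% power, 3 df |
|---|---|---|---|---|---|
| A | 19.87 | 2.81 | 80.3% | 48.6% | 84.6 |
| B | 18.82 | 2.97 | 84.4% | 52.5% | 80.1 |
| C | 17.77 | 3.15 | 88.2% | 56.9% | 75.6 |

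A simulation of reading A (200,000 runs) gave 48.8%.

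**4. Sensitivity, all with 3 df.**
- No dropout (25 per unit): 52.3%, 55.9% and 60.8% on readings A, B and C.
- Baseline adjustment, with an assumed correlation r acting at both unit and individual level (SE of reading A × √(1 − r²)): 59% at r = 0.5, 66% at r = 0.6, 74% at r = 0.7.
- True effect of 29.9 min/day: 19% on reading A and 20% on reading B. The normal formula would give 32–36%.

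**The case against.** **The arithmetic is right and clustering is allowed for.** Both statements stand. A reader might infer that the plan ignores clustering or miscalculates 200. It does neither: the design effect uses the unit ICC, and 200 reproduces exactly. What is missing is an allowance for the small number of units.

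**The planned analysis may be more efficient than an unadjusted comparison.** This also stands in part. The article collects a baseline and three follow-ups and plans mixed models with covariates, so "about 50%" should not be read as the power of whatever analysis is finally run. It is the power of the unadjusted comparison, which is all the sample-size paragraph takes credit for. Assumed baseline correlations up to 0.7 still leave power at 74%, and a unit-level covariate would cost a further degree of freedom.

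**A mixed model on individual data need not use 3 df.** With individual-level degrees of freedom the nominal power on reading A is about 80%, but only because eight units are treated as many, which inflates the type I error. A model that drops the unit variance when it is estimated at zero reaches only 51–54%, with type I error of about 5.5%.

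**The degrees-of-freedom method belongs in the SAP.** The choice of method may. The power figure and the number of units are both stated in the article, however, and no later choice of method adds units.

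**The assumed effect.** The Development section reports a pooled result for multicomponent digital interventions, "presenting a reduction of 29.9" min per 8 h workday. A reader might infer that 55.92 is therefore wrong. The documents do not show that: the two figures are on different bases (per 8 h workday and per day), the source for 55.92 is not at hand, and choosing a target effect is a judgement. The comparison supports a sensitivity figure only.

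**Significance out of reach.** A reader might also infer that four pairs can never give a significant result. That would concern a within-pair randomisation test, and the article plans linear mixed models.

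**Conclusion.** The point holds. The 80% is a large-sample figure attached to a design with four company pairs. On the plan's own inputs, with 20 completers per unit and company or country in the model, power at 55.92 min/day for an unadjusted comparison is about 49–53%, and 57% on the most favourable reading of the two ICCs. Power of 80% needs a difference of about 80–85 min/day (about 76 on that most favourable reading). No alternative examined that keeps valid error control restores 80%: full retention gives at most 61%, and baseline adjustment gives 59–74% under assumed correlations of 0.5–0.7. The result rests on the stated SD and unit ICC, on equal unit sizes, and on testing the effect against between-unit variation.

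**What to change.** **Restate the sample-size paragraph.** State that the trial has eight units in four company pairs and that the treatment contrast has about 3 degrees of freedom. Replace 80% with the range: about 49–53% at 55.92 min/day unadjusted (up to 57% on other ICC readings), and 80% only at about 80–85 min/day. If credit is taken for baseline adjustment, give the assumed correlation and its source. Optionally, show power at 29.9 min/day (about 19–20%) as a sensitivity figure. This costs wording only.

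**An option only if units are not yet fixed.** Randomising four smaller units per company (two per arm, 12–13 people each) keeps 200 participants and gives 16 units and 16 − 4 − 1 = 11 degrees of freedom. With 10 completers per unit and residual share 1 − ICC, power at 55.92 is about 84% at a unit ICC of 0.05, 78% at 0.08, 74% at 0.10 and 65% at 0.15. Smaller teams may be more alike, so the higher ICCs matter. There are other costs. Each company must have four separable units that can each supply enough volunteers, while the eligibility criteria ask only for different units. Contamination may also rise: unit-level allocation is there to limit it, and the app's challenges and chat are described as company-wide.
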